### 2.2. Sample Size, Randomization, and Allocation

A sample of 96 participants (48 per group) is needed for an 80% probability to identify a difference between the treatment and control group. The power analysis for the sample size estimation was based on the means, standard deviations, and clinical cut-off for the primary outcomes (RTS, TSDS; Williams et al., 2022c, 2023b). Drawing on previous research, we hypothesized a standard mean difference of between 0.36 and 0.52, between the treatment and control group, which translates to a 10–20% decrease in the primary outcomes (i.e., RTS, TSDS) for individuals at the endpoint of treatment. Given these effect estimates, with an alpha of 0.05, an 80% power, and a 20% attrition, we estimated a sample size of approximately 96 (48 per group) will be needed. This randomized controlled trial will use an ANOVA and t-test (alpha error level = 5%, two-sided) for independent samples.

This sample size will require tailored recruitment efforts, community partnerships, and culturally safe retention strategies throughout the trial. Given differential attrition rates for racialized communities, the research team will spend additional time at intake discussing barriers to participation, issues with attendance, and address any participant concerns. Additionally, the research team will offer flexible session meeting times (e.g., evenings and weekends), and telephone check-ins as needed. The research team shall also compensate participants for both their completed sessions and batteries of measures.

In terms of blinding, the trial research team will be unaware of the group allocation. This includes the principal investigator and project coordinator who are overseeing the trial implementation, research assistants who will support recruitment and data collection, and the statistician conducting the analysis. See Figure 1 for the participant flow diagram of the trial.

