Moreover, the research team will use targeted emails, social media posts, local bus ads, and word of mouth to advertise the study, instructing interested individuals to reach out to a study-specific email address. Once interest is confirmed, an email response will be sent with detailed information about the study and a consent form for consideration. The said study-specific email address will also present a direct contact with whom prospective participants may communicate should they have any questions or concerns about the study. Those interested in moving forward will be invited to partake in a 3 h virtual intake session (See Table 1 for the participants’ assessment schedule). During this intake, a trained research assistant will (i) describe important elements of the study, including the participant’s role and responsibilities; (ii) collect the necessary information from the participant to start a “file” (e.g., date of birth, gender, occupation, ethnoracial identity, contact information, emergency contact); (iii) and administer two semi-structured diagnostic interviews (i.e., the Mini International Neuropsychiatric Interview as well as the University of Connecticut Racial/Ethnic Stress & Trauma Survey). A 15 min break will be provided at the halfway point of the intake session. Using this intake information, the research team will continually and iteratively assess the demographic characteristics of the enrolled participants, gender and otherwise, to ensure sample heterogeneity and the generalizability of the findings (e.g., age, ethnicity, immigrant status, and socioeconomic status). Participant personal information and identifiers will be stored in a data management system to ensure participant privacy protection and data security. Data used for analysis will only include unique identification numbers assigned to each participant at intake. The data will be published in aggregate form and no participant identifier will be included.

Following intake, the participants will be randomly assigned to one of two groups: the HRTP (intervention) group or the control group (TAU). The randomization will be conducted using a computer-generated randomization sequence with stratification by age, gender, and the baseline level of racial stress (via the Racial Trauma Scale; Williams et al., 2022b).

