### 2.12. Statistical Analysis

Descriptive statistics, including means, standard deviations, and frequencies, will be calculated for continuous primary and secondary outcomes. Differences in primary and secondary outcomes, including TSDS, RTS, change in symptoms, and therapeutic experiences, will be examined using a two-way mixed ANOVA with two or three within-subject levels of time (pre-test, post-test, and follow-up) and two between-subject levels of condition (HRTP and control). When there is evidence of sphericity violation, we will use the Greenhouse–Geisser correction (Greenhouse & Geisser, 1959). It is predicted that participants’ TSDS and RTS scores will decrease significantly over the course of the treatment. It is also predicted that TSDS and RTS scores at follow-up will be the same or lower than at the end of the treatment.

Both the short-term and long-term efficacy of the HRTP will be examined during the treatment (week 0, 4, 8), at the end of the treatment (week 12), and 4 months after the treatment (week 28). Assessment will take place at four time points for the treatment group (HRTP therapy; weeks 0, 4, 8, 12, and 28; see Table 1 for participants’ assessment schedule) and only two time points for the control TAU group (T0 and T4; see Table 1 for participants’ assessment schedule). Analysis will compare standard mean differences (SMDs) between the time points for the treatment group (weeks 0, 12, and 28) and the control group (weeks 0 and 12). Analyses will entail intent to treat (ITT) and include participants with pre-treatment and the last time point available as long as they attended at least one treatment session. We examine significant levels for the analysis as well as effect sizes. A significance level of *p* < 0.05 will be used for all tests.

For each outcome of interest, we will identify any significant Condition × Time interactions. When no interaction is found, significant main effects will be reported. Partial eta-squared (η2) was used to measure effect sizes for the ANOVAs. When significant interactions are found, post hoc tests of simple main effects will be used to examine the differences, *p* values will be included for all post hoc tests, and 95% confidence intervals (CIs) will be used for all *p* values less than 0.05. Additionally, we will conduct comparisons of baseline data for completers and non-completers. Subgroup analysis will be based on age, gender, and levels of racial stress and trauma.

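### If the Condition × Time interaction is null, the plan reports main effects without saying they are not evidence of efficacy; the interaction itself uses the baseline inefficiently

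*Protocol article*

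**What the plan says.** Section 2.12 (Statistical Analysis) specifies a two-way mixed ANOVA with time as the within-subject factor (pre-test, post-test and, where available, follow-up) and condition as the between-subject factor. The Condition × Time interaction is examined first. Then: "When no interaction is found, significant main effects will be reported". Every test uses p < 0.05. The section predicts that TSDS and RTS scores will fall significantly during treatment, and this prediction does not mention the control arm. In the sentence on post hoc tests after a significant interaction, "95% confidence intervals (CIs) will be used for all" p values below 0.05.

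Section 2.9 and Table 1 show that TAU is assessed only at weeks 0 and 12. Week 28 exists for HRTP alone.

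Section 2.2 says that the trial "will use an ANOVA and t-test (alpha error level = 5%, two-sided) for independent samples". Section 2.3 randomises "with stratification by age, gender, and the baseline level of racial stress". In Section 2.12 these factors return only for subgroup analysis. Section 2.4 assigns each participant a therapist; the stated model has no therapist term.

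**The concern.** Section 2.1 declares a superiority trial, so the question is whether HRTP changes scores more than TAU does. With two shared visits, that contrast is the interaction. The fallback comes into play exactly when this contrast is not significant, and nothing in Section 2.12 limits how the reported main effects may be read.

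- **Time.** This is improvement averaged over the two arms. It is expected even if HRTP adds nothing: participants enter with clinically relevant symptoms (Section 2.3), and TAU is 12 sessions of evidence-based therapy (Section 2.7).
- **Condition.** This averages the week-12 score with a score taken before randomisation. It therefore dilutes the effect and brings in chance baseline imbalance.

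A significant time effect after a null interaction would appear to confirm the non-comparative prediction in Section 2.12. Separately, the interaction gives away precision that data already collected could supply.

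**Working it through.** **Inputs.** From Section 2.2: "we hypothesized a standard mean difference of between 0.36 and 0.52, between the treatment and control group"; "with an alpha of 0.05, an 80% power, and a 20% attrition"; 48 per arm. After 20% attrition, 48 × 0.8 = 38.4, taken as 38 per arm. Assumed, because the article does not give them: equal SD (= 1) at weeks 0 and 12, pre-post correlation r of 0.5 to 0.7, and improvement common to both arms of 0.3 or 0.5 SD. Power uses the normal approximation.

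**The plan's own sample size.** n per arm = 2(1.96 + 0.842)²/SMD², divided by 0.8.
- SMD 0.52: 59 per arm, 74 after inflation, total 148.
- SMD 0.36: 122 per arm, 153 after inflation, total 306.

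The stated 96 is not reproduced from the stated inputs. It can be reached if a correlation is assumed, for example ANCOVA at SMD 0.52 with r = 0.6 (38 per arm, 48 after inflation). That is a separate matter, but it means there is little precision to spare.

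**Time main effect when HRTP adds nothing.** SD of change = √(2(1 − r)); SE = SD/√76. The interaction is null in 95% of trials and is essentially independent of the time effect.
- 0.5 SD improvement, r = 0.5: SE = 1/√76 = 0.115, ratio 4.36, power 99%; 0.95 × 0.99 = 94%.
- 0.5 SD improvement, r = 0.7: SE = 0.775/√76 = 0.089, ratio 5.6, power above 99.9%; about 95%.
- 0.3 SD improvement: 70% (r = 0.5) or 87% (r = 0.7).

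Simulation (8,000 trials, 38 per arm) gave 94.3%, 95.3%, 69.9% and 87.0%.

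**Condition main effect.** Expected value = (0 + SMD)/2; SD = √((1 + r)/2).
- SMD 0.52, r = 0.5: effect 0.26, SE = 0.866 × √(2/38) = 0.199, ratio 1.31, power 25.7%. At r = 0.6 and 0.7 it is 24.4% and 23.2%.
- SMD 0.36, r = 0.5: 14.6%.
- With equal variances the change and the mean of the two scores are uncorrelated. Counting either test as a finding therefore gives 1 − 0.95² = 9.75% under the null (simulated 9.4-9.9%).

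**Interaction against ANCOVA.** With two visits the interaction test equals the t-test on change scores, with variance proportional to 2(1 − r). For ANCOVA it is 1 − r². The ratio is 2/(1 + r).

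| r | Variance ratio | SMD 0.52: interaction / ANCOVA | SMD 0.36: interaction / ANCOVA |
|---|---|---|---|
| 0.5 | 1.33 | 62.0% / 74.5% | 34.8% / 44.1% |
| 0.6 | 1.25 | 71.7% / 80.9% | 41.9% / 50.1% |
| 0.7 | 1.18 | 83.3% / 88.8% | 52.6% / 59.4% |

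**Therapist clustering.** Design effect = 1 + (m − 1) × ICC for m clients per therapist. The article gives neither m nor the ICC. Purely as illustration, m = 3 to 8 and ICC = 0.02 to 0.10 give 1.04 to 1.70, and a nominal 5% test would then run at about 5.5% to 13.3%.

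**The case against.** The plan looks at the interaction first, which is the right randomised test. Section 1.4 hypothesises larger changes than in control, and the fallback sentence says only that main effects are reported, not that they show efficacy. All of this stands. The 94-95% is thus not a false-positive rate for a declared claim; it is how often the plan would put a significant result with no treatment content next to a null comparison. Likewise the condition effect is diluted rather than spurious, and 9.75% applies only if it is counted as a finding. The change-score test is valid under randomisation, so ANCOVA is a gain in efficiency, and its size depends on an unstated correlation.

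Stronger readings are tempting but not supported:

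- *The model ignores baseline.* It does not: pre-test is a level of time. The fault is inefficient use.
- *Leaving out therapist wastes precision.* The direction is the opposite: it can overstate precision. The phrase "ANOVA and t-test (alpha error level = 5%, two-sided) for independent samples" attaches independence to the t-test and is no decision about clustering. A therapist term and covariates may stand in an analysis plan that is not shown.
- *Standard errors are certainly too large because age and gender are omitted.* That requires these factors to predict outcome, which the article does not show.
- *No interval would be given for a null treatment effect.* The CI clause concerns post hoc tests, and partial eta-squared is promised separately. The article simply does not commit to an interval for the main contrast.

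**Conclusion.** The point holds for the fallback rule, which is written in the article and cannot be attributed to a missing document. Neither main effect can replace a null interaction. The time effect would be significant beside a null interaction in about 94-95% of trials under a common 0.5 SD improvement (70-87% at 0.3 SD) with no HRTP benefit. The condition effect has about 25% power at SMD 0.52 and opens a second route to a false positive.

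The efficiency point also holds, as an improvement rather than a correction of an invalid test. Change-score variance exceeds ANCOVA variance by 33%, 25% or 18% at r = 0.5, 0.6 or 0.7, worth roughly 12, 9 or 6 percentage points of power at SMD 0.52. These sizes rest on assumed correlations, equal variances at the two visits and 38 analysed per arm. Therapist clustering is secondary, and its size cannot be computed from the documents.

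**What to change.** 1. Delete the main-effects sentence, or state that main effects are descriptive and not evidence of efficacy.
2. For each primary outcome (RTS, BDI-II, TSDS), make the efficacy test the HRTP minus TAU difference at week 12 from ANCOVA. Adjust for the outcome's continuous baseline value and the stratification factors: age, gender and, for BDI-II and TSDS, baseline RTS as well.
3. Report that difference with its 95% CI whatever the p value.
4. Label pooled and within-arm change as uncontrolled, including the week-28 maintenance result, which exists for HRTP only. The maintenance objective in Section 1.4 can still be reported on that footing.
5. Record therapist ID and account for clustering in the model or in a sensitivity analysis.

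Cost: wording, one extra identifier, a few degrees of freedom, and possibly a slightly wider interval from the therapist term. No additional participant assessments are needed.

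### Post hoc confidence intervals are tied to p < 0.05, so no interval is planned for any non-significant comparison, including the one meant to show that gains are maintained

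*Protocol article*

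**What the plan says.** Section 2.12 (Statistical Analysis) of the protocol article sets two reporting branches after the two-way mixed ANOVA.

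- **Interaction significant.** "When significant interactions are found, post hoc tests of simple main effects will be used to examine the differences". For these tests p "values will be included for all post hoc tests", with no condition attached, whereas "95% confidence intervals (CIs) will be used for all" p values below 0.05.
- **Interaction not significant.** "When no interaction is found, significant main effects will be reported". Nothing is said about estimates or intervals for main effects that are not significant.

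The same section plans means and SDs for continuous outcomes, standardised mean differences between time points, and partial eta-squared, which "was used to measure effect sizes for the ANOVAs". It adds: "We examine significant levels for the analysis as well as effect sizes". None of these depends on significance, and none comes with an interval. Confidence intervals are mentioned nowhere else in the article.

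The section also predicts that RTS and TSDS scores at follow-up will be no higher than at the end of treatment. Section 2.2 (Sample Size, Randomization, and Allocation) gives 96 participants (48 per group), 80% power, 20% attrition, hypothesised standardised mean differences (SMDs) of 0.36 to 0.52, and an "ANOVA and t-test (alpha error level = 5%, two-sided) for independent samples".

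**The concern.** A confidence interval is most useful when a result is not significant, because it separates a trial that has ruled out a worthwhile effect from one that was too imprecise to tell. The article reverses this: significant post hoc contrasts get an interval, and the others do not. This is a written rule, so it would have to be changed and not merely supplemented.

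Two results are exposed.

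- **The week-12 comparison between arms.** This is the core efficacy question. If it is not significant, on either branch, no interval is planned for it.
- **Maintenance from week 12 to week 28.** Table 1 shows that only the HRTP arm is assessed at week 28, so this is a within-arm contrast. Support for unchanged scores would appear as a non-significant difference, the class for which the rule gives no interval. Without one, a non-significant change could be read as proof of maintenance when the data still allow a sizeable loss of benefit.

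**Working it through.** **1. What the text covers**

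| Situation | p value | 95% CI |
|---|---|---|
| Interaction significant, post hoc p < 0.05 | planned | planned |
| Interaction significant, post hoc p ≥ 0.05 | planned | excluded by the rule |
| No interaction, main effect significant | effect reported | not mentioned |
| No interaction, main effect not significant | not mentioned | not mentioned |

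No non-significant row has a planned interval.

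**2. The stated sample size**

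Inputs from section 2.2: two-sided alpha 0.05, 80% power, SMD 0.36–0.52, 20% attrition. For two means, n per arm = 2(1.960 + 0.842)² / SMD².

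- SMD 0.52: 59 per arm, 118 in total. With attrition, 59/0.8 gives 74 per arm, 148 in total.
- SMD 0.36: 122 per arm, 244 in total. With attrition, 122/0.8 gives 153 per arm, 306 in total.

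The stated 96 is not reproduced from these inputs. That is a separate point. It is used here only because it makes non-significant results more likely.

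**3. Precision and power (illustration only)**

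Assumptions: two-sample t-test on post-treatment scores, SD = 1, and n = 48 (no loss) or 48 × 0.8 ≈ 38 per arm. Half-width = t(0.975, 2n − 2) × √(2/n).

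- n = 48: 1.986 × 0.2041 = 0.41 SD
- n = 38: 1.993 × 0.2294 = 0.46 SD

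Power from the noncentral t distribution, noncentrality SMD × √(n/2):

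| n per arm | SMD 0.36 | SMD 0.52 |
|---|---|---|
| 48 | 42% | 71% |
| 38 | 34% | 61% |

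The chance of a non-significant result is therefore 29%–58% with 48 per arm and 39%–66% with 38.

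Example: an observed SMD of 0.20 with 38 per arm has the interval 0.20 ± 0.46, or −0.26 to 0.66. It contains zero and the whole hypothesised range. In simulation with 38 per arm, the upper limit exceeded 0.52 in about 85% (true SMD 0.36) to 94% (true SMD 0.52) of non-significant trials. With 48 per arm the figures were about 80% and 91%.

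**4. Sensitivity to the pre–post correlation**

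The article gives no correlation r. Change-score variance is 2(1 − r) times the post-score variance, so r = 0.5 reproduces step 3. With 38 per arm (normal approximation):

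- r = 0.3: power 26%–48%
- r = 0.7: power 53%–83%, so 17%–47% of trials would still be non-significant

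**5. The maintenance contrast (illustration only)**

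Within the HRTP arm, half-width = t(0.975, n − 1) × √(2(1 − r)/n). Here r is the assumed week 12–28 correlation.

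- n = 38, r = 0.5: 2.026 × √(1/38) = 0.33 SD
- n = 38, r = 0.3: 2.026 × √(1.4/38) = 0.39 SD
- n = 38, r = 0.7: 2.026 × √(0.6/38) = 0.25 SD
- n = 48, r = 0.5: 2.012 × √(1/48) = 0.29 SD

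With 38 analysed and r = 0.5, an observed change of exactly zero would still allow a worsening of 0.33 SD, close to the lower hypothesised benefit of 0.36.

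**The case against.** The strongest objection is about scope. The CI clause belongs to post hoc simple-effect tests, which run only after a significant interaction. A null interaction falls under a different sentence, which does not forbid intervals. A condensed article may leave such detail to an analysis plan. This stands. A reader might infer that the article bans an interval for a null primary result, or that the clause would withhold one in 39%–66% of trials. The documents support neither. The first is unstated, and the percentages come from an unconditional t-test, not from the setting in which the clause operates.

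Second, non-significant contrasts do not get only a p value. Means, SDs, SMDs and partial eta-squared are planned without a significance condition, so a reader could rebuild the week-12 interval for post-treatment scores. This also stands, in part. A within-arm or change contrast needs the correlation between time points, which is not among the planned summaries, and partial eta-squared carries no direction. For the same reason, a reader might infer that only inflated, significant estimates would be published. That does not follow, because point estimates are not restricted to p < 0.05.

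Third, the planned mixed ANOVA uses baseline, and the ITT rule keeps participants with a last available time point. Power could therefore exceed the 38-per-arm figures. This is correct, and it is why both sample sizes and a range of correlations are shown. At r = 0.7, significance is the likelier outcome across the hypothesised range.

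**Conclusion.** The point holds as a reporting rule that is fixed badly. Among post hoc tests, a 95% CI depends on p < 0.05. In the no-interaction branch only significant main effects are to be reported. Together these leave every non-significant comparison without a planned interval. The text alone supports this, whatever the power.

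How much it matters depends on assumptions. Under a post-score t-test, the missing interval would have a half-width of about 0.41 to 0.46 SD, and a non-significant result has a chance of 29%–58% (48 per arm) or 39%–66% (38 per arm) at the hypothesised effects. That is a substantial risk. It is more likely than not at SMD 0.36 on these assumptions, but not at 0.52. These figures show how imprecise a null result would be; they do not measure how often the clause takes effect. The maintenance prediction is the clearest casualty, because the result that would support it is the kind the rule leaves without an interval.

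**What to change.** In section 2.12, delete the p < 0.05 condition on confidence intervals and replace the two reporting sentences with one rule: for every primary and secondary between-arm comparison and every post hoc contrast, including week 12 to week 28 in the HRTP arm, report the estimated difference with its 95% CI from the planned model, whatever the p value and whatever the interaction test shows.

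This needs no change of model or estimand; whether to adjust for baseline is a separate question. The cost is a sentence or two of text, with no extra data, visits or staff time. It should be made before the data are analysed.

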This trial will use a stratified randomization process to incorporate study covariates (i.e., age, gender, and racial stress levels) each with 2 categories for a total of 6 strata. While transgender and gender non-conforming people account for 0.3% of Canada’s population (Statistics Canada, 2022), the trial will oversample this population because of low attrition rates and the reality of gender minority populations being traditionally excluded in clinical research (Adams & Miller, 2022; Owen-Smith et al., 2016). We will evaluate and report any gender differences in response to treatment and outcomes through subgroup analysis to consider the intersectionality of minoritized individuals (e.g., Adams & Miller, 2022).

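### The blanket p < 0.05 rule covers the age, gender and racial-stress subgroup analyses, so chance differences could be reported as differential response

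*Protocol article*

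**What the plan says.** The protocol article deals with subgroups in two places.

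- Section 2.12, last sentence of the analysis of primary outcomes: "Subgroup analysis will be based on age, gender, and levels of racial stress and trauma".
- Section 2.3, on stratification and gender: "We will evaluate and report any gender differences in response to treatment and outcomes through subgroup analysis".

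The rule on significance is in section 2.12 and has no exception: "A significance level of *p* < 0.05 will be used for all tests". Section 2.2 adds that testing is two-sided.

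The model in section 2.12 is a two-way mixed ANOVA of time by condition, and the interaction to be looked for on each outcome is Condition × Time. The post hoc sentence gives p-values for all post hoc tests, but 95% confidence intervals only where p is below 0.05.

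Section 2.3 names age, gender and baseline racial stress as the stratification factors, with two categories each. Section 2.9 names three primary outcomes (RTS, BDI-II, TSDS).

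**The concern.** Read together, these statements put the subgroup analyses under the same significance rule as the primary comparison. The stated model has no term for a difference in effect between subgroups. Intervals may also be missing where a result is not significant, which is where a reader most needs them to see that two subgroups overlap.

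Section 2.3 promises a statement about who responds differently. In a trial of 96, chance alone can produce such a difference, and a real one of plausible size would usually be missed. What is at stake is a published claim that HRTP works better for one gender, age group or severity level, in the communities the trial means to serve, when the data cannot support it.

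**Working it through.** **Inputs from the article.** 96 randomised, 48 per arm, 20% attrition, SMD 0.36 to 0.52, two-sided alpha 0.05 (section 2.2); three factors (section 2.12); two categories per factor (section 2.3, where they are strata); three primary outcomes (section 2.9).

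**Assumptions not in the article.** The subgroups are the stratification categories; levels are balanced; factors are independent; outcomes correlate 0.3 to 0.7; the pre-post correlation ρ is 0.5, with a range shown where it matters.

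**The plan's own figure.** The article gives no power or error figure for subgroups. Its only sample-size figure, 96, is for the overall comparison, and it does not follow from the stated inputs. At SMD 0.52, n per arm = 2 × (1.96 + 0.84)² / 0.52² ≈ 58.05, so 59 per arm or 118 in total, and 118 / 0.8 ≈ 148 with attrition. That is a separate matter. Here 96 is used only as the number of participants.

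**Step 1: size of a subgroup level.** 48 × 0.8 = 38.4, so about 38 analysed per arm and 38 / 2 = 19 per arm in each level. If all 96 are analysed, it is 24.

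**Step 2: false differences if effects are compared by interaction.** With no true heterogeneity, each test has a 5% false-positive rate.
- Three factors, one outcome: 1 − 0.95³ = 14.3%. Simulation gives about 14%.
- Three factors, three outcomes: 1 − 0.95⁹ = 37.0% if independent. Allowing for correlated outcomes, simulation gives 35.3%, 34.7% and 29.3% at correlations of 0.3, 0.5 and 0.7, and about 31% at 0.6 in a separate simulation.

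**Step 3: power of one interaction test.** For two time points, Condition × Time is a comparison of change scores. In units of the single-time SD, the standard error of the difference between two level-specific effects is √(4/19) × √(2(1 − ρ)). The detectable difference at 80% power is 2.80 × SE, and power is Φ(0.52/SE − 1.96) for a difference of 0.52 SD.

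| ρ | SE | Detectable interaction | Power for 0.52 SD |
|---|---|---|---|
| 0.3 | 0.543 | 1.52 SD | about 16% |
| 0.5 | 0.459 | 1.29 SD | about 20% |
| 0.7 | 0.355 | 1.00 SD | about 31% |

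With all 96 analysed and ρ = 0.5, power is about 24%. Unequal levels would lower all of these.

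**Step 4: if levels were instead tested separately.** This is conditional, because the article does not say so. It takes the SMD as the effect on the analysed scale.
- With 19 per arm, power within a level is 0.191 at SMD 0.36 and 0.345 at 0.52. If the true effect is the same in both levels, the chance that exactly one is significant is 2p(1 − p): 2 × 0.191 × 0.809 = 31% and 2 × 0.345 × 0.655 = 45%, for one factor and one outcome.
- Chance of that pattern for at least one factor, by simulation with outcome correlation 0.6:

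| Analysed | Outcomes | SMD 0.36 | SMD 0.52 |
|---|---|---|---|
| 76 | one | 52% | 70% |
| 76 | three | 77% | 92% |
| 96 | one | 58% | 74% |
| 96 | three | 83% | 94% |

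- With no treatment effect at all, at least one level is significant in about 21% (one outcome) to 44% (three outcomes) of trials.

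**The case against.** **Missing detail in a condensed article.** The subgroup test, its rank and an exploratory label are commonly left to the full protocol or analysis plan, neither of which is shown. This stands, and their absence alone would not be a finding. What remains is text the article does fix: a threshold that "will be used for all tests", a single named interaction, intervals tied to significance, and the commitment in section 2.3.

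**Separate testing is not stated.** A reader might infer that each level will be tested separately, so that a false finding of benefit in one group only is likely. The documents do not support this. No section describes separate testing, and the section 2.3 wording on differences in response fits an interaction at least as well. The figures of 52–94% therefore hold only if levels are tested separately and the true effect is uniform. A false-positive interaction is also not the same as benefit confined to one group.

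**Per-test versus family-wise rates.** A reader might set the 30–35% against 5% and call it a seven-fold breach. That comparison is unsound: 0.05 is a per-test level, and the article claims no family-wise rate for subgroups. Nor does it say that the subgroup analyses cover all three primary outcomes, so nine tests is an upper case.

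**Mitigating facts.** The factors are few, pre-specified and the same as the randomization strata, and the hypotheses in section 1.4 concern only the overall effect and its maintenance. This limits data-driven searching and means no efficacy claim rests on a subgroup. It neither raises power nor takes the subgroup tests out of the all-tests rule.

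**Analysed numbers.** The intent-to-treat rule in section 2.12 keeps participants with a last available time point after at least one session, so more than 38 per arm may be analysed. Using all 96 changes power only from about 20% to 24%.

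**Conclusion.** The point holds in a limited form. As worded, section 2.12 treats subgroup tests as ordinary significance tests, and section 2.3 promises to report differences in treatment response by gender. On the more favourable reading, interaction tests, about 14% of trials (three tests, one outcome) to about 30–35% (nine tests, three outcomes) would show at least one false subgroup difference. A true difference of 0.52 SD, the top of the planned range for the main effect, would be detected only about 20% of the time at ρ = 0.5 and about 31% at ρ = 0.7. The detectable interaction is about 1.3 and 1.0 SD respectively.

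These figures rest on balanced, independent two-level factors and 38 analysed per arm. The documents do not show that a misleading result in one group only is likely. That would need separate testing within levels, which they leave open. The change is worth making because it corrects stated rules at almost no cost.

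**What to change.** **Section 2.12**
- Limit the p < 0.05 rule to the primary condition comparisons.
- State that the analyses by age, gender and racial stress are exploratory.
- Base each on the treatment-by-subgroup interaction at week 12 in the full sample. Week 12 is the only post-baseline time at which both arms are assessed.
- Report the interaction estimate and the effect in each level with a 95% confidence interval, whatever the p-value.

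**Section 2.3**
- Describe the gender analysis as exploratory estimation of the treatment-by-gender interaction.

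**Cost.** Wording in two sections and a few extra model terms, with no change to design or sample size. The downside is that subgroup results cannot be claimed as confirmed, which a trial of this size could not support in any case. Interaction tests alone would not be enough: without the exploratory label or an adjustment, the 14% to 30–35% false-positive rates remain.
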